# Effectiveness of pulmonary rehabilitation for patients with asthma: study protocol of a randomized controlled trial (EPRA)

**DOI:** 10.1186/s12890-017-0389-3

**Published:** 2017-03-09

**Keywords:** Pulmonary rehabilitation, Asthma, RCT, Longitudinal study, Asthma control, ACT, Inpatient rehabilitation, Randomized controlled trial, Longitudinal, Economic evaluation

## Abstract

**Background:**

Asthma patients are enrolled in multimodal pulmonary rehabilitation (PR) programs. However, available data for the effectiveness of PR in asthma are sparse. Therefore, the primary aim of this randomized control trial (RCT) is to evaluate short-term (end of rehabilitation) and intermediate-term effectiveness (3 months after rehabilitation) of PR for patients with asthma regarding asthma control (primary outcome) and other outcomes. Secondly, moderator effects of gender, age, baseline asthma control, quality of life, and anxiety will be examined. Thirdly, a longitudinal follow-up study will explore the course of the outcomes over one year and the annual costs.

**Methods:**

The EPRA study is a single-center randomized controlled waiting-list trial in the Bad Reichenhall Clinic. Inclusion criteria include a referral diagnosis for uncontrolled asthma, no cognitive impairment and no very severe co-morbidities that indicate significantly greater illness morbidity than asthma alone. In the intervention group (IG), participants will start PR within 4 weeks after randomization; participants of the control group (CG) will start PR 20 weeks after randomization. Data will be assessed at randomization (T0), after 4 weeks (T1; IG: begin of PR), 7 weeks (T2; IG: end of PR), and 20 weeks (T3, CG: begin of PR). The primary outcome is asthma control at T2/T3. Secondary outcomes are health-related quality of life, functional exercise capacity, dyspnea, anxiety, depression, subjective self-management skills, illness perceptions, sick leave and subjective work ability. Outcomes will be analyzed with analysis of covariance, including baseline values of the respective outcomes as covariates. Healthcare costs will be analyzed with a gamma model with a log-link.

A longitudinal follow-up study will generate additional data at 3/6/9/12 months after PR for both IG and CG. Latent change models will be used to analyze the course of the primary and secondary outcomes. Annual cost differences before and after rehabilitation will be compared by paired t-test.

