### Study aims

The primary aim of this RCT is to evaluate the effectiveness of PR for patients with asthma on short (end of rehabilitation) and intermediate-term (3 months after rehabilitation) outcomes as compared to a waiting-list control group. We hypothesize that pulmonary inpatient rehabilitation is superior regarding mean change in AC at 3 months after rehabilitation (primary outcome). Furthermore, we expect superior effectiveness of the pulmonary rehabilitation regarding health related quality of life (HRQoL), functional exercise capacity, dyspnea, anxiety, depression, subjective self-management skills, illness perceptions, sick leave, as well as subjective work ability (secondary outcomes). In addition, moderator effects of (a) gender, (b) age, (c) baseline AC, (d) baseline HRQoL and (e) baseline anxiety will be examined. Moreover, in a longitudinal follow-up study, the course of primary and secondary outcomes over one year and the annual costs before and after rehabilitation will be explored.

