## Methods

### Study design and data collection

We use a two part-study design, combining a randomized controlled trial (RCT) and a longitudinal follow-up design.

The main study is a randomized control superiority trial, comparing the intervention group (IG) with a waiting-list control group (CG). For legal reasons, any insurant of the statutory German Pension Insurance (GPI) whose application for medical rehabilitation was approved by the GPI will receive a rehabilitative intervention. Therefore, it is not possible to use an entirely untreated CG, but a waiting-list CG can be realized. After inpatient rehabilitation in the Bad Reichenhall Clinic has been approved by the GPI, patients receive a letter informing about the study and screening for their eligibility. If no response is received within 14 days, a reminder will be sent to the patients. If patients meet the inclusion criteria, they are asked to participate. After consent has been obtained, participants will be randomized to the IG or CG. In the IG, participants will start inpatient rehabilitation within 4 weeks after randomization. Data will be assessed at randomization (T0), at the beginning (T1), the end (T2), and three months after inpatient rehabilitation (T3). The CG will start inpatient rehabilitation five months (i.e. 20 weeks) after randomization. CG data will be assessed at randomization (T0), at four weeks (T1), at seven weeks (T2) and at 20 weeks (T3, beginning of inpatient rehabilitation) after randomization. The crucial reference intervals for the primary research questions are T0 to T2 and T0 to T3 for both IG and the CG. Since CG starts PR 19 to 20 weeks after T0, which is 3 months after the discharge time-point of IG, it will be possible to compare the results of IG with those of the (still) untreated CG during these initial 19 to 20 weeks. However, it may be possible that for the CG, arrival at the rehabilitation clinic (at T3) already has an effect on several outcome parameters. To estimate this “arrival effect”, an additional measurement time point (T3a) for the CG at 10 (+/-3) days before T3 has been included.

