### Sample size

Calculation of sample size is based on our primary outcome, the ACT, assessed three months after the inpatient rehabilitation. A previous longitudinal study of asthma patients in the Bad Reichenhall Clinic (without a CG) showed changes between start of inpatient rehabilitation and three months after inpatient rehabilitation of (Cohen’s) d > 0.5 [25]. However, this value might overestimate the effect of inpatient rehabilitation compared to a control group. Therefore, sample size was calculated to detect a difference of d = 0.3 at T3 between the IG and CG. Using alpha = 0.05 and power = 0.8, 352 participants are required, but assuming a drop-out rate of 30%, a total of n = 504 patients will be recruited [26].

Latent curve models will be used to analyze the course of the primary outcome in the longitudinal follow-up study. As a rule of thumb, N > 100 cases should be included in the computation of these models. Even with a conservatively estimated drop-out rate of 50% until T6 for IG and T8 for CG, N = 152 patients would remain in the study, which is sufficient.

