### Outcomes and measures

The primary outcome is the mean change in AC, assessed by ACT. Secondary outcomes include mean changes in HRQoL, 6-min walk distance (6-MWD) and Sit-to-stand-test, lung function parameters, Eosinophils, dyspnea, depression, anxiety, smoking habits, illness representations, self-management skills, work ability, subjective prognosis of return to work, sick leave, medication beliefs and medication adherence. Measurement instruments for all outcomes and measurement occasions can be found in Table 1. Lung function parameters, 6-MWD, FeNO, and Eosinophils are assessed at the start and the end of the inpatient rehabilitation by staff of the PR. All other outcomes are assessed via questionnaires.

**Table 1 Tab1:** outcome measures

Outcome	measured by/Instrument	T0	T1	T2	T3A (CG)	T3	T4	T5	T6	T7 (CG)	T8 (CG)
Asthma control	Asthma control test (ACT) [29, 30]	X	X	X	X	X	X	X	X	X	X
Lung function, blood gases	FEV1, FEV1/VC, SRtot, VC, RV, PaO2, PaCO2, [50, 51]		IG	IG		CG	CG				
Exercise capacity	6MWT [53]										
Allergy	Total Ig E, specific Ig E-Screening (ImmunoCAP®)		IG	IG		CG	CG				
Asthmatic inflammation	Fractional exhaled nitric oxide (FeNO) [56], Eosinophils		IG	IG		CG	CG				
QoL	Saint George’s Respiratory Questionnaire (SGRQ) [35]	X	X	X	X	X	X	X	X	X	X
QoL	Asthma Quality of Life Questionnaire (AQLQ)] [36]	X	X	X	X	X	X	X	X	X	X
QoL	EQ-5D-5L [37, 38, 57]	X	X	X	X	X	X	X	X	X	X
QoL	Global Rating of Change Scale (GROC-scale) [39]			X	X	X	X	X	X	X	X
Symptoms	Numerical rating scale for dyspnoea, cough, sputum, pain [40]	X	X	X	X		X	X	X	X	X
Dysfunctional breathing	Nijmegen Questionnaire (NQ) [58]	X	X	X	X					X	X
Depression	Patient Health Questionnaire (PHQ) [59]	X	X	X	X		X	X	X	X	X
Anxiety	Generalized Anxiety Disorder Questionnaire (GAD 7) [60]	X	X	X	X		X	X	X	X	X
Fatigue	Brief Fatigue Inventory (BFI) [41]	X	X	X	X						
Illness Perception	Illness Perception Questionnaire (IPQ-R) German Version [45]	X	X	X	X		X	X	X	X	X
Resource Use	FIM-Lu, modification of FIMA [52]	X			X		X	X	X	X	X
Work ability	Work Ability Index (WAI) Items 1 and 4 [61]	X	X	X	X		X	X	X	X	X
SPoRTW	SPE-Scale [55]	X	X	X	X		X	X	X	X	X
Self-management	Health Education Impact Questionnaire (heiQ), Scale “Skill and technique acquisition”	X	X	X	X		X	X	X	X	X
Smoking habits	Questionnaire (developed)	X			X		X	X	X	X	X
Sport behaviour	Questionnaire (developed)	X			X		X	X	X	X	X
Medication beliefs	Brief Medication Questionnaire (BMQ) [62]	X	X	X	X				X	X	X

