### Assessment of outcomes

#### Asthma control

Asthma Control will be assessed by using the Asthma Control Test (ACT) [30, 33]. The ACT consists of five items that assess (1) activity limitation, (2) daytime shortness of breath, (3) awaking due to asthma symptoms, (4) needed puffs of reliever medication and (5) a global judgment of asthma control. All items refer to the last 4 weeks. They are scaled from 1 to 5. The sum of scores indicates asthma control. An ACT score of 20 – 25 indicates controlled asthma and of <20 indicates uncontrolled asthma. A minimal important difference about 3 was identified [34].

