### Statistical methods

Primary and secondary outcomes will be analyzed according to the intention to treat approach [56]. All randomized patients will be included in the analysis. Missing data fulfilling the assumption of missing (completely) at random will be imputed using multiple imputation procedures [57]. In addition, because it may be possible that some patients will not start with the inpatient rehabilitation or decide to drop-out of the study, we will also analyze results based on a “per protocol” approach [58, 59] including only patients remaining in the study until T3.

The analysis of the primary and secondary outcomes at T2/T3 will use analysis of covariance (ANCOVA) with treatment group as a fixed effect and baseline value of the respective outcome as a covariable. Adjusted mean differences and confidence intervals will be reported. In addition, moderating effects [60] of the following baseline variables on the primary outcome will be analyzed: ACT, gender, age, quality of life (assessed via SGRQ Total Score), anxiety (assessed using GAD-7) and depression (assessed using PHQ-7). For all models, statistical model assumptions (linearity, homoscedasticity, normality of residuals) will be tested. If model assumptions are violated, appropriate analysis methods (e.g. robust regression, log-transformation) will be used.

Latent change models will be used for exploratory analyses of the course of the primary and the secondary outcomes in the follow-up longitudinal study [61, 62].

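### The primary endpoint is asthma control at T2 and T3 in the abstract but at T3 alone in the hypothesis and sample size; the stated alpha and power together fit only T3

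*Protocol article*

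**What the plan says.** Two places in the protocol article attach the primary question to two time points:

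- Abstract, Methods: "The primary outcome is asthma control at T2/T3".
- Study design and data collection: "The crucial reference intervals for the primary research questions are T0 to T2 and T0 to T3 for both IG and the CG".

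The abstract's Background points the same way in its primary aim, which is to "evaluate short-term (end of rehabilitation) and intermediate-term effectiveness (3 months after rehabilitation) of PR". The opening sentence of Study aims is equally broad.

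Two places make T3 the only primary time point:

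- Study aims, in the hypothesis: rehabilitation is expected to be "superior regarding mean change in AC at 3 months after rehabilitation (primary outcome".
- Sample size: "Calculation of sample size is based on our primary outcome, the ACT, assessed three months after the inpatient rehabilitation". The target difference of d = 0.3 is also set at T3.

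Two places do not settle the matter:

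- Outcomes and measures gives no time point: "The primary outcome is the mean change in AC, assessed by ACT".
- Statistical methods gives one method for both visits without saying which is primary: "The analysis of the primary and secondary outcomes at T2/T3 will use analysis of covariance (ANCOVA".

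On timing, the abstract places T2 at week 7, the end of rehabilitation for the intervention group (IG), and T3 at week 20. The Intervention section gives a 3-week programme. The ACT description says "All items refer to the last 4 weeks".

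**The concern.** A reader who wants to know later whether the reported primary result was the planned one gets different answers from different sections. A benefit seen at T2 but not at T3 would be a primary success under the abstract and a primary failure under the hypothesis. The headline conclusion could then depend on which section is cited once the results are known.

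The error rates are also at stake. One undivided alpha of 0.05 and one power of 0.8 are stated. If two time points are primary, the meaning of those figures depends on whether success at one is enough or success at both is needed.

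**Working it through.** **Inputs.** From Sample size: d = 0.3 at T3, alpha = 0.05, power = 0.8, 352 evaluable, 30% drop-out, 504 recruited. Sidedness and allocation ratio are not stated; two-sided and 1:1 are inferred because they reproduce 352. The correlation r between the T2 and T3 test statistics is not in the article. It is assumed here and shown over a range.

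**Step 1: reproduce the plan's figure.** Normal approximation, per arm:

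n = 2 × (1.960 + 0.842)² / 0.3² = 174.4, so 175 per arm and 350 in total.

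The exact two-sided t-test gives 175.4, so 176 per arm and **352** in total. A one-sided test gives 276 and does not match. For drop-out, 176 / 0.7 = 251.4, so 252 per arm and **504** in total. The design is therefore sized for one test at T3 using the whole two-sided 0.05.

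**Step 2: two primary time points.** Let Z₂ and Z₃ be the test statistics at T2 and T3, jointly normal with correlation r.

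- Either suffices: familywise error = 1 − P(|Z₂| < 1.96, |Z₃| < 1.96), both means zero. With independence this is 1 − 0.95² = 0.0975.
- Both required: joint power = P(Z₂ > 1.96, Z₃ > 1.96), each mean 2.80, which is 80% power for each test. The article gives no effect size at T2, so 80% power there is an assumption.

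| Assumed r | Familywise error, either suffices | Joint power, both required |
|---|---|---|
| 0.3 | 0.0951 | 0.666 |
| 0.5 | 0.0907 | 0.687 |
| 0.7 | 0.0835 | 0.713 |
| 0.8 | 0.0781 | 0.729 |

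With exactly 176 per arm and d = 0.3 at both visits, each mean is 0.3 × √88 = 2.81, and the last column becomes 0.671, 0.692, 0.717 and 0.733. When both are required, type I error stays at or below 0.05.

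**Step 3: the price of keeping both, with either sufficient.** Bonferroni at 0.025 each: n = 2 × (2.241 + 0.842)² / 0.3² = 211.2, so 212 per arm and 424 in total (426 by the t-test). At 30% drop-out this is about 606 to 610 recruited. With 352 evaluable, power per test would fall to about 0.71 to 0.72.

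**Step 4: what ACT covers at each visit.** On the nominal schedule the IG is in the clinic from week 4 to week 7.

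- T2 (week 7): recall covers weeks 3 to 7. For the IG that is about one week before admission plus the 3-week stay, with no time after discharge. For the control group (CG) it is waiting time.
- T3 (week 20): recall covers weeks 16 to 20, wholly after rehabilitation for the IG and before it for the CG.

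**The case against.** The best defence is that the two operative statements, the hypothesis and the sample size, agree on T3. Only the abstract names both visits as the primary outcome. The design section speaks of primary research questions in the plural and names no endpoint. The ANCOVA sentence gives a method for all outcomes at both visits. This stands in part: the ANCOVA sentence cannot be counted as evidence for two primaries, and T3 is clearly the better-supported reading. It does not remove the contradiction, because the abstract's sentence cannot be read as T3 alone.

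Three stronger readings are tempting, and the article does not support them.

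- A reader might infer that type I error *is* inflated. It would be only if success at either visit counted, and no section says so. With T3 alone the error is 5%. With both required it is at most 5%, and the loss is in power.
- A reader might infer that a multiplicity rule is missing. This is a condensed article and the analysis plan is not shown. Test order and alpha allocation may be set out there, so their absence is not the point. The point is the conflicting endpoint labels.
- A reader might infer that T2 is an invalid measure. The article presents T2 as an end-of-rehabilitation measure, and a score that mostly covers the stay can register change during it. Inpatient care against waiting is the randomized contrast itself. The recall overlap limits what T2 can be said to show; it does not disqualify it.

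T3 has its own caution, which the article already raises: arrival at the clinic may affect the CG's answers at T3. The additional T3a measurement is there to estimate that.

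**Conclusion.** The point holds as an inconsistency in the definition of the primary endpoint. The abstract and the design section point to T2 and T3; the hypothesis and the sample size fix T3. The stated alpha of 0.05 and power of 0.8 hold together only for a single primary test at T3.

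The size depends on the reading. There is no effect on error rates if T3 alone is primary. Familywise error is about 7.8% to 9.5% if either visit suffices, and joint power about 0.67 to 0.73 if both are required. These ranges rest on assumed correlations of 0.3 to 0.8, and the power figures also on assumed 80% power at T2. Two-sided testing and 1:1 allocation are inferred from reproducing 352.

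The recall window is a supporting reason to prefer T3 as primary and a caution for interpreting T2, no more.

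**What to change.** Name one primary endpoint, ACT at T3 adjusted for the T0 value and tested at two-sided 0.05, and use that definition everywhere. The places to align are the abstract (Background and Methods), Study design and data collection, Outcomes and measures, and Statistical methods. The hypothesis and the Sample size section already agree with it.

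List ACT at T2 as a secondary endpoint for short-term effect. Testing it only after a significant T3 result is optional. Add a sentence where T2 is interpreted: for the IG, the score describes about one week before admission and the inpatient stay, with no time after discharge.

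The change is wording only; 352 evaluable, 504 recruited and alpha of 0.05 are unchanged. The downside is that a benefit seen only at T2 can no longer be reported as a primary success. If the sponsor does want both visits primary, the success rule must be stated and its cost accepted: about 606 to 610 recruited under Bonferroni, or the lower joint power if both are required.

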**Discussion:**

This RCT will determine the effectiveness of a complex inpatient PR for asthma patients concerning asthma control. Furthermore, important medical and economic information regarding the effectiveness of PR as part of the long-term management of patients with uncontrolled asthma will be generated.

**Trial registration:**

German Clinical Trials Register (DRKS00007740, May 15, 2015). Protocol version: 1.0 (December, 23, 2016).

## Background

### Introduction

Asthma is one of the most common chronic diseases worldwide with an estimated 300 million affected individuals [1]. Asthma was defined by the Global Initiative for Asthma (GINA) as a heterogeneous disease, usually characterized by chronic airway inflammation and a history of respiratory symptoms that vary over time and in intensity, including wheeze, shortness of breath, chest tightness and cough, together with variable expiratory airflow limitation [1]. Thus, the diagnosis of asthma is primarily based on clinical symptoms [2]. In spite of the availability of effective medications, it remains incurable. Various cross-sectional studies have shown a high number of patients with poorly controlled asthma in many countries [3, 4]. Therefore, new approaches to improve asthma control (AC) are urgently required.

Pulmonary rehabilitation (PR) is widely accepted as an effective treatment for patients with chronic respiratory diseases, especially for chronic obstructive pulmonary disease (COPD) [5]. In Europe and North America, asthma patients are also commonly enrolled in PR programs [6], but the available data regarding the effectiveness of PR for asthma patients are sparse. Only very few randomized studies [7, 8] concerning the effectiveness of a multimodal PR program in asthma have been published. All had certain methodological limitations, so that they weren’t considered for international evidence-based asthma guidelines [1, 2].

However, the effectiveness of the essential individual components of PR, such as patient education [9, 10], respiratory physiotherapy [11, 12] and aerobic exercise training [13–18] has been shown in several randomized controlled trails (RCTs). As a complete PR program is expected to be at least as effective as these single components, the German National Disease Management Guideline [19] recommends PR for asthma patients if physical, mental or social consequences of the illness are constraining and persist during daily life despite adequate medical therapy.

Besides the two RCTs [7, 8], a limited number of observational studies have been published in the international [20–24] and German literature [25–27]. They have shown positive effects regarding quality of life, clinical symptoms, physical function, exacerbations, and health care resource utilisation. However, up to now, no RCTs have addressed the question whether and how long asthma control improves after PR. Therefore, such a study was strongly recommended by the German National Disease Management Guideline [19].

This lack of evidence is of particular relevance since asthma is a common indication for PR in Europe and in the US [6], and is the most frequent indication for PR in Germany [28]. Therefore, the main objective of the EPRA-RCT is to fill the knowledge gap for PR in asthma. Moreover, there is little empirical data regarding the long-term course of AC, quality of life and self-management skills after PR for asthma and the cost-effectiveness. As part of the EPRA study a follow-up assessments at 6, 9 and 12 months after PR will be provided.

### Study aims

The primary aim of this RCT is to evaluate the effectiveness of PR for patients with asthma on short (end of rehabilitation) and intermediate-term (3 months after rehabilitation) outcomes as compared to a waiting-list control group. We hypothesize that pulmonary inpatient rehabilitation is superior regarding mean change in AC at 3 months after rehabilitation (primary outcome). Furthermore, we expect superior effectiveness of the pulmonary rehabilitation regarding health related quality of life (HRQoL), functional exercise capacity, dyspnea, anxiety, depression, subjective self-management skills, illness perceptions, sick leave, as well as subjective work ability (secondary outcomes). In addition, moderator effects of (a) gender, (b) age, (c) baseline AC, (d) baseline HRQoL and (e) baseline anxiety will be examined. Moreover, in a longitudinal follow-up study, the course of primary and secondary outcomes over one year and the annual costs before and after rehabilitation will be explored.

